**Methods:**

A double-blinded, 2-arm feasibility trial of 48 participants (24 per group) comparing VRMM+NTR and VR sham+NTR will be conducted. Recruitment, retention, adherence, and acceptability outcomes will be collected throughout the trial. Injury-related fear will be measured using the 11-Item Tampa Scale of Kinesiophobia. Jump-landing biomechanics will be assessed via peak knee abduction moment and peak knee flexion excursion. The change in outcomes will be compared between groups using 2×2 repeated measures ANOVA and partial η^2^ effect sizes. Significance will be set at *P*<.05.

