### Statistical Analysis

Descriptive statistics (means, SD, frequency, and ranges) will be calculated for recruitment, retention rates, adherence, and acceptability outcomes. A threshold of 75% or better will be used as the minimum threshold for acceptable recruitment, adherence, and retention outcomes. A threshold of 50% will represent moderate acceptability, and scores of 80% or better will be used to identify high acceptability [40].

Descriptive statistics will be calculated for participant demographics, TSK-11 scores, peak knee abduction moment, and knee flexion excursion. A 2×2 repeated measures ANOVA will be used to assess changes between the intervention and sham groups. Group and time will serve as our independent variables. The TSK-11 score, peak knee abduction moment, and knee flexion excursion will serve as our dependent variables. The results will be reported as means and mean differences, with 95% CIs, *F*-values (ratio of between-group variance to within-group variance), and *P* values. The significance level will be set at a corrected value of *P*<.02 to reflect multiple comparisons (0.05/3). We hypothesize that patients in the VRMM+NTR group will demonstrate lower injury-related fear, decreased external knee abduction moment, and increased knee flexion excursion when compared to the VR sham+NTR group. Hypotheses for each outcome will be tested independently. We believe that these statistical differences will be supported with moderate to strong effect sizes. Partial η^2^ effect sizes will be calculated to examine the magnitude of the Group × Time interaction. Effect sizes will be interpreted as small if between 0.01 and 0.08, medium if between 0.09 and 0.24, and large if >0.25 [47].

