### Limitations and Anticipated Problems

This trial is designed to assess the feasibility and preliminary efficacy of VRMM in patients after ACLR. Therefore, we will not be able to draw any firm conclusions regarding the effectiveness of the VRMM intervention to improve the measured outcomes in this population. A larger randomized clinical trial will be needed to investigate the efficacy of VRMM+NTR compared to VR sham+NTR. The results from this trial will determine whether such a study is feasible and how a fully powered clinical trial may be optimally designed for this purpose.

Additionally, there are a total of 26 participant visits from preassessment to postassessment involved in this trial. Therefore, it is possible that participants may drop out, miss a study visit/visits, or that there may be missing data, which would introduce a risk of attrition bias. The feasibility outcomes are being used to understand these factors, and our sample size was calculated to account for possible attrition. Finally, the TSK-11 scale will be interpreted cautiously in view of the limitation that the scale was not developed specifically for acute musculoskeletal injuries; however, psychometric properties suggest that this scale can be applied to help understand outcomes after ACLR [42].

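### Magnitude is read from uncorrected partial eta-squared against fixed bands: at 40 to 48 participants it runs about 0.02 too high, and it is not separate support for a significant P value

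*Protocol article*

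**What the plan says.** All of the following is in the protocol article.

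- **Model** (Statistical Analysis): "A 2×2 repeated measures ANOVA will be used to assess changes between the intervention and sham groups". The three dependent variables are the TSK-11 score, peak knee abduction moment and knee flexion excursion.
- **Significance level**: Statistical Analysis sets P < .02, as 0.05 divided by three outcomes. The Methods paragraph of the Abstract differs: "Significance will be set at *P*<.05".
- **Measure of magnitude** (Statistical Analysis): partial eta-squared "effect sizes will be calculated to examine the magnitude of the Group × Time interaction".
- **Bands** (Statistical Analysis): "Effect sizes will be interpreted as small if between 0.01 and 0.08, medium if between 0.09 and 0.24, and large if >0.25".
- **Expected role** (Statistical Analysis): "We believe that these statistical differences will be supported with moderate to strong effect sizes".
- **Other reporting** (Statistical Analysis): means and mean differences with 95% CIs, F values and P values. No interval is stated for partial eta-squared.
- **Use of the results** (Limitations and Anticipated Problems): no firm conclusion on effectiveness will be drawn, and the trial is to show "how a fully powered clinical trial may be optimally designed for this purpose".

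**The concern.** Two properties of partial eta-squared matter at this sample size.

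First, it cannot be negative, so chance alone gives it a positive average when there is no effect. If the lowest band starts below that average, a verbal label of *small effect* is a common result of pure noise.

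Second, for an interaction with one numerator degree of freedom it carries the same information as the F statistic and its P value. If the smallest value that a significant result can take already lies in the medium band, saying that the effect size supports the significant difference states the same finding twice.

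At stake is how the aim 2 results are described. The trial disclaims firm conclusions on effectiveness, so its description of magnitude is a large part of what aim 2 passes on to the design of the next trial.

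**Working it through.** **Inputs.** Two groups and two time points, so Group × Time has 1 and N − 2 degrees of freedom. N = 40 is the evaluable number and N = 48 the recruited number in Sample Size Estimation and Study Population. Significance levels and bands are as quoted. The bands leave small gaps (0.08 to 0.09, 0.24 to 0.25), so I use cut-points of 0.01, 0.09 and 0.25.

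**The plan's own figure.** The document gives no figure for bias or for the smallest significant effect size. The nearest is the sample size: 40 in total for 80% power at partial eta-squared 0.23 and two-sided alpha 0.05. A noncentral F calculation with λ = N·η²/(1 − η²) gives N = 30 for those inputs and 92.0% power at N = 40. The stated 40 is reached at alpha 0.05/3 (82.4% power). That is a separate matter. This check takes only the values of N from there.

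**Step 1: link to the P value.** Partial η² = F/(F + N − 2).

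| Level | N | Critical F | Smallest partial η² if significant |
|---|---|---|---|
| .02 | 40 | 5.90 | 5.90/(5.90 + 38) = 0.134 |
| .02 | 48 | 5.81 | 5.81/(5.81 + 46) = 0.112 |
| .05/3 | 40 | 6.27 | 0.142 |
| .05/3 | 48 | 6.17 | 0.118 |
| .05 (Abstract) | 40 | 4.10 | 0.097 |
| .05 (Abstract) | 48 | 4.05 | 0.081 |

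At P < .02 every significant result is medium or larger. At the Abstract's P < .05 this holds at N = 40 but just fails at N = 48.

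**Step 2: no true effect.** Partial η² then follows a Beta(1/2, (N − 2)/2) distribution with mean 1/(N − 1): 1/39 = 0.026 and 1/47 = 0.021. A value of 0.01 corresponds to F = 0.01 × 38/0.99 = 0.384 at N = 40 and 0.01 × 46/0.99 = 0.465 at N = 48. The chance of exceeding it is 54% and 50%. These shares count all labels from small upward.

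**Step 3: true effect present.** Means from simulated noncentral F values, using partial ω² = (F − 1)/(F − 1 + N) and partial ε² = (F − 1)/(F + N − 2):

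| True value | N | Mean partial η² | Mean ω² | Mean ε² |
|---|---|---|---|---|
| 0 | 40 | 0.026 | 0.000 | 0.000 |
| 0 | 48 | 0.021 | 0.000 | 0.000 |
| 0.03 | 40 | 0.054 | 0.029 | 0.029 |
| 0.03 | 48 | 0.050 | 0.029 | 0.030 |
| 0.09 | 40 | 0.112 | 0.086 | 0.088 |
| 0.09 | 48 | 0.108 | 0.087 | 0.089 |

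The upward bias is 0.018 to 0.026 over this range, and the corrected versions remove nearly all of it.

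**Step 4: effect on labels.** With ω² in the bands, a null outcome is labelled small or more in 24% (N = 40) or 23% (N = 48) of cases, against 54% or 50%. For true values from 0 to 0.09, the label changes in 22% to 32% of outcomes.

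**Step 5: what correction does not do.** At a true 0.09 and N = 40, results with P < .02 average 0.209 on partial η² and still 0.185 on ω². At the P = .02 boundary ω² is 0.109 (N = 40) or 0.091 (N = 48), still medium. The 95% CI for the population value at that boundary runs from 0.002 to 0.33 (N = 40) or from 0.002 to 0.29 (N = 48), which a bare label hides.

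**The case against.** The case against is substantial, and much of it stands.

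- **The sentence about support is an expectation, not a rule.** It follows the hypotheses, and nothing in the section makes partial eta-squared a second test. This stands. The sentence is misleading, but it drives no decision in that section.
- **Raw magnitude is already planned.** Mean differences with 95% CIs will be reported, and effect sizes are not made conditional on P. This stands and limits the harm. But the section assigns the magnitude of the interaction to partial eta-squared and its bands, with no interval stated.
- **The bias is small.** About 0.02 is modest beside the planning value of 0.23. It is not small beside a band that starts at 0.01 or a medium cut-point of 0.09.
- **The corrected measures are functions of the same F.** True: they are no more independent of P than partial eta-squared. They cure the bias, not the redundancy, so the wording has to go as well.
- **The measure matches the power calculation and the bands have a cited source.** That explains the choice but does not alter its behaviour at this sample size.

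A reader might infer that the next trial will be badly undersized because significant effect sizes are strongly inflated. The document does not support that. It nowhere says that the next trial will be sized from an estimate picked for its significance.

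**Conclusion.** The point holds as one about estimation and wording. Partial eta-squared overstates the interaction by about 0.02 for true values of 0 to 0.09. The bands label about half of truly null outcomes small or more. At P < .02 the medium-or-larger label follows from arithmetic, so it adds nothing to the P value.

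This rests on 40 to 48 analysed participants, one numerator degree of freedom, normal-theory F distributions and the cut-points above. A 20% loss from 48 would leave about 38, where the figures are slightly worse (smallest significant value 0.141, null mean 0.027). The guarantee depends on the level in Statistical Analysis and does not fully carry over to the Abstract's P < .05.

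Two stronger readings should be avoided. The guarantee is medium *or larger*, not medium: at N = 40 and a true 0.09, about 22% of significant results exceed 0.25. And a corrected estimator does not cure the inflation among significant results, because that inflation comes from selection.

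**What to change.** In Statistical Analysis:

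1. Report partial omega-squared or epsilon-squared with a 95% CI for the Group × Time term of all three outcomes, whatever the P value, and apply the bands to that estimate.
2. Delete the statement that effect sizes will support the statistical differences.
3. State that magnitude is read mainly from the between-group difference in change, in outcome units, with its 95% CI. I take this to be among the mean differences already planned; one clause would make it explicit.
4. State that planning of the next trial will use the unselected estimate and its CI.

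The example of promising efficacy in Rationale and Principal Findings (partial eta-squared of at least 0.09) should then say which statistic it refers to.

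The cost is one formula, an interval and a few sentences. Data collection, conduct and sample size do not change. The downside is slightly smaller printed effect sizes. With 12 participants randomized so far, the change can be made well before the analysis.

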### Ethical Considerations

This study obtained ethical approval from the UNC-CH institutional review board through the Office of Human Research Ethics (22‐0493). The study is funded by the National Institute of Arthritis and Musculoskeletal and Skin Diseases (K23AR079056-04). The trial was registered on ClinicalTrials.gov on September 2, 2022, and most recently updated on April 14, 2025 (NCT05527171). Recruitment began on September 5, 2023, and will be completed by approximately May 31, 2027.

Participants will be assigned a study ID to protect identifiable data (ie, VRMM_001 to VRMM_048). All signed consent forms will be locked in the principal investigator’s office, separate from all other study data. Study data will be stored in the REDCap (Research Electronic Data Capture) system, a secure web application provided by the North Carolina Translational and Clinical Sciences Institute for building and managing case report forms. Data and forms checking and double data entry will be conducted, with final data quality control performed by the principal investigator.

Adverse events will be recorded throughout the trial and will be reported in aggregate to the safety officer and National Institute of Arthritis and Musculoskeletal and Skin Diseases as part of routine data safety monitoring reports. Intentional unblinding will occur only for the participant’s safety when a serious adverse event occurs. The principal investigator and the safety officer will be notified of any serious adverse events.

## Results

The study was funded in May 2021. The trial started in September 2023 and is anticipated to be completed in May 2027, with first results expected to be submitted for publication in winter 2027. As of now, 55 participants have been screened for eligibility, of whom 33 were ineligible (Figure 2). Twelve participants have been randomized, and 10 have completed the trial (Figure 2). Two participants withdrew from the trial before the completion of the full intervention protocol due to the study time commitment.

## Discussion

### Rationale and Principal Findings

Psychological factors related to sports-related injuries and, specifically, outcomes after ACLR have recently garnered increased attention. Importantly, the influence of elevated injury-related fear has been linked to return-to-sport failures, decreased physical activity, and higher secondary injury rates [4,9,48]. Therefore, interventions are needed to address injury-related fear after ACLR. However, psychologically informed rehabilitation strategies for patients after ACL injury and reconstruction are still in their infancy. Systematic reviews have compiled a handful of articles investigating psychological interventions after ACLR, which include guided imagery and relaxation, web-based support, coping modeling videos, therapeutic insight videos, and neurocognitive rehabilitation approaches [49,50]. These reviews reveal a small amount of low-quality evidence, suggesting that psychological interventions can improve short-term outcomes (ie, self-reported injury-related fear and pain) compared to standard rehabilitation [49].

We propose a methodologically rigorous, low risk-of-bias study to address the concerns in the literature regarding the low-quality evidence supporting psychological interventions to improve outcomes after ACLR. This study will contribute to this growing area of research in psychological interventions to improve health outcomes after ACLR by investigating the use of VRMM in addition to standard neuromuscular rehabilitation in a randomized trial in patients after ACLR. While all participants will experience the VR headset and NTR, we expect to see superior results in patients who are exposed to the active ingredients: guided mindfulness including focused attention, breathing awareness techniques, and mindful movement.

Furthermore, we are following the NIH stage model’s systematic framework for behavioral intervention development to guide our study. This study is in stage 1 as we primarily aim to identify the feasibility of our intervention. However, we are optimistic that the results from this study will allow our research team to transition into stage 2 to evaluate the efficacy of the VRMM intervention in a traditional efficacy research study. We expect to move forward with the development of a larger-scale clinical trial if our hypotheses are supported regarding recruitment, retention, adherence, and acceptability and if promising preliminary efficacy for outcomes in aim 2 is observed (eg, Partial η^2^ ≥0.09). Following the procedures outlined in the NIH stage model will allow our team to develop a highly potent and maximally implementable behavioral intervention to improve clinical outcomes in patients after ACLR.

### Limitations and Anticipated Problems

This trial is designed to assess the feasibility and preliminary efficacy of VRMM in patients after ACLR. Therefore, we will not be able to draw any firm conclusions regarding the effectiveness of the VRMM intervention to improve the measured outcomes in this population. A larger randomized clinical trial will be needed to investigate the efficacy of VRMM+NTR compared to VR sham+NTR. The results from this trial will determine whether such a study is feasible and how a fully powered clinical trial may be optimally designed for this purpose.

Additionally, there are a total of 26 participant visits from preassessment to postassessment involved in this trial. Therefore, it is possible that participants may drop out, miss a study visit/visits, or that there may be missing data, which would introduce a risk of attrition bias. The feasibility outcomes are being used to understand these factors, and our sample size was calculated to account for possible attrition. Finally, the TSK-11 scale will be interpreted cautiously in view of the limitation that the scale was not developed specifically for acute musculoskeletal injuries; however, psychometric properties suggest that this scale can be applied to help understand outcomes after ACLR [42].

### Conclusion

To the best of our knowledge, this feasibility trial will be the first study to investigate the use of VRMM in the post-ACLR population. The effect of this intervention will be compared to a sham group, and both groups will simultaneously receive standard-of-care neuromuscular rehabilitation. Outcomes of interest include the feasibility of the trial, acceptability of the intervention, self-reported injury-related fear, and jump-landing biomechanics. The results of this trial will improve our understanding of how psychological interventions may be used to address injury-related fear in females after ACLR.
